### Participant timeline

The individual participant timeline is depicted in Fig. 1. Study duration for each patient comprises 14 months. This includes the period of eight months intervention and a post-intervention follow-up period of six months. Table 1 shows the four assessment time points during the study (T0, T1, T2, T3). Assessment time point T(− 1) is assigned to the time point of initial admission to inpatient or day-hospital care.

### Sample size

The sample size estimation is based on data from our pilot study [26], where we observed a difference of 1.09 BMI points with a standard deviation of 2.0 in the experimental condition. We conservatively assume a BMI increase of 0.1 BMI points in the TAU-O group with an effect size of 0.495, even though in the literature a stable BMI or a slight decrease was observed under comparable conditions in TAU groups [18, 22]. Therefore, 66 evaluable patients are necessary in each study arm (software query 7.0). To adjust for 30% dropouts, we will recruit 95 patients per study arm, i.e. 190 patients in all. We have based our conservative estimation of the dropout rate of 30% on our pilot trial [26] where we observed 25% dropout. Recent RCTs investigating novel treatments for AN report dropout rates ranging from 20 to 30% [22, 30]. Note that the sample size was calculated for a simple t-test of differences, whereas the primary analysis will be an ANCOVA with baseline adjustment. We expect a decrease of the standard error due to this procedure which will more than compensate the loss of one degree of freedom by inclusion of the covariate and the loss of eight degrees of freedom by inclusion of centre as stratification factor.

### Randomization

Eligible patients will be randomized in equal proportions between the aftercare intervention SUSTAIN or TAU-O. Randomization takes place after completion of the baseline assessment (T0) and is performed independently by the Institute for Clinical Epidemiology and Applied Biostatistics, Tübingen, Germany (ICEAB). Randomization is stratified according to trial site. The ICEAB informs the respective trial site investigator about the group assignment.

### Blinding

Our study design does not allow us to implement blinding of therapists and patients. The study personnel performing the data assessment will be blinded.

### Data management and data monitoring

All data is assessed pseudonymized. Independent data management is provided by the Institute for Clinical Epidemiology and Applied Biometry, Tübingen, Germany (ICEAB). We use electronic case report forms provided by the electronic database secuTrial© (www.secutrial.com) which is access controlled, audit-trailed and certified for Good Clinical Practice (GCP-ICH). Data will predominantly be entered electronically by either the study personnel or patients themselves for self-report measures. Some data will be derived from paper-based source data and transferred to the electronic database; fidelity to the source data will be monitored. Data management will also comprise regular plausibility checks of data entries.

The Centre of Clinical Trials (ZKS Tübingen) at the University Hospital Tübingen is responsible for quality assurance in the present trial and performs regular structured data monitoring in accordance with a fixed monitoring manual. The monitoring procedure includes an initiation visit, intermediate monitoring and a close-out visit. The data monitoring focuses on validation of written informed consent, documentation of (severe) adverse events, validation of inclusion and exclusion criteria, data validity of outcome measures with a special focus on source data transfer and documentation of end of treatment and study dropout.

### Statistical methods

This is an efficacy trial with the primary aim to show superiority of a specialized post-inpatient psychotherapy vs. TAU-O. The primary endpoint (BMI) will be analysed using a baseline (= end of inpatient treatment T0) adjusted ANCOVA for BMI measurement at the end of post-inpatient psychotherapy (T2) with study centre as nuisance factor included. The primary analysis population is the intent-to-treat population (ITT) with imputation of missing data for drop-outs. It is expected that endpoints might be obtained from at least a subsample of drop-outs which might improve the accuracy of imputation procedures for subjects with missing outcome data. Secondary analyses include a linear mixed model for overall course of BMI using BMI at T(− 1) and at T0 as covariates and T1, T2, T3 as dependent observations with predefined analysis: interaction of group with contrasts T2-T1, T3-T1, and (T3 + T2)/2-T1 and estimation of adjusted mean and 95% CI for T3-T2, chi-square test and logistic regression for proportion of relapse. The remaining secondary endpoints will be analysed using adequate methods (chi-square test and logistic regression for binary outcomes, t-test and linear models for continuous outcomes). Time to drop-out will be analysed as a secondary endpoint, using Kaplan Meier and Cox proportional hazard regression. Safety will be analysed using tabulations and line listings of adverse events and separately of severe adverse events. Selected results including the primary endpoint will be analysed in the per protocol (PP) population. We will perform moderator analyses using interaction terms of therapy with potential moderator variables. No interim analysis is planned.

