#### Primary outcome measure

We chose Body Mass Index (BMI) in kg/m^2^ as our primary outcome measure. BMI is of high clinical relevance, as especially early weight loss after inpatient discharge predicts course of AN [37]. Recent large RCTs investigating efficacy of treatments for AN have used BMI as primary outcome [28, 30, 38], including the two most recent trials investigating a post-inpatient psychotherapy [18, 22]. Current treatment guidelines for EDs across different countries and health care systems emphasize that weight gain and reaching a healthy BMI are key goals of AN treatment [14].

BMI will be calculated based on body height measurement and recurrent measures of body weight at the trial site. The primary efficacy endpoint is the change in BMI between baseline (T0) and end of treatment (T2) eight months later adjusted for baseline BMI.

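### The primary ANCOVA is valid but leaves out admission BMI, a baseline value in hand for every patient that could add a little precision at almost no cost

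*Protocol article*

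**What the plan says.** Under Primary outcome measure: "The primary efficacy endpoint is the change in BMI between baseline (T0) and end of treatment (T2) eight months later adjusted for baseline BMI". Under Statistical methods, the primary model is a T0-"adjusted ANCOVA for BMI measurement at the end of post-inpatient psychotherapy (T2) with study centre as nuisance factor included". Its covariates are therefore T0 BMI and centre.

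The next analysis in the same section is described thus: "Secondary analyses include a linear mixed model for overall course of BMI". It is fitted "using BMI at T(− 1) and at T0 as covariates", with T1, T2 and T3 BMI as the outcomes. So T2 BMI is an outcome in both models, and T(-1) BMI is a covariate in only one.

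Under Participant timeline, T(-1) "is assigned to the time point of initial admission to inpatient or day-hospital care". The inclusion criteria require a rise of at least one BMI point over the stay, which cannot be checked without an admission value. T(-1) BMI is thus measured before randomisation and should be complete.

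**The concern.** Adjusting for a prognostic pre-randomisation covariate reduces the residual variance, and so the standard error of the treatment effect, without introducing bias. T0 and T(-1) together also carry the amount of weight regained in hospital. Two patients discharged at the same BMI, one after a small gain and one after a large one, look identical to the primary model. The sponsor evidently thinks T(-1) BMI may be informative about BMI after discharge, since it is a covariate in the mixed model. The article gives no reason for using it there and not in the confirmatory test. What is at stake is some precision in the primary comparison, not its validity.

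**Working it through.** **1. Reproduce the planned sample size.** Under Sample size: "we observed a difference of 1.09 BMI points with a standard deviation of 2.0 in the experimental condition" and "We conservatively assume a BMI increase of 0.1 BMI points in the TAU-O group with an effect size of 0.495". Effect size = (1.09 − 0.1)/2.0 = 0.495. The article states neither alpha nor power; two-sided alpha 0.05 and 80% power are assumed. A two-sample t-test then needs 66 per arm (power 80.6%; 65 per arm gives 79.98%), as stated. Dropout: 66/0.70 = 94.3, so 95 per arm and 190 in all, also as stated. This calculation takes no credit for any covariate.

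**2. Power of the current ANCOVA.** With 132 evaluable patients, error df = 132 − 2 − 1 (T0) − 8 (centre) = 121. Keeping the residual SD at 2.0, that is, giving T0 no credit, the noncentrality is 0.495 × √(66/2) = 2.84 and power is 80.5%.

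**3. Add T(-1) BMI.** Let r be the partial correlation of T(-1) with T2 BMI given T0 BMI and centre. Residual variance is multiplied by 1 − r², the effect size becomes 0.495/√(1 − r²), and error df falls to 120. The values of r are assumptions.

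| r | 1 − r² | Fall in SE | Power |
|---|---|---|---|
| 0 | 1.00 | 0% | 80.5% |
| 0.1 | 0.99 | 0.5% | 80.9% |
| 0.2 | 0.96 | 2.0% | 82.1% |
| 0.3 | 0.91 | 4.6% | 84.1% |
| 0.4 | 0.84 | 8.3% | 86.8% |

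**4. The cost.** There are two ways to count it.
- *Error df only, as in the table.* At r = 0, power goes from 80.54% to 80.53%, a loss well under 0.1 point.
- *Also charging chance imbalance of the new covariate between arms.* The expected variance of the treatment effect rises by a factor of about 1 + 1/119 = 120/119, or 0.84%. The net factor is (1 − r²) × 120/119, which equals 1 when r² = 1/120, so r ≈ 0.09. On this count, putting 0.495/√(120/119) = 0.493 into the same formula gives 80.2% at r = 0, a loss of about 0.3 point. The powers at r = 0.1, 0.2 and 0.3 become 80.6%, 81.8% and 83.8%.

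**5. If T0 BMI already does much of the work.** Suppose T0 adjustment removes a quarter of the variance (correlation 0.5). The effect size is then 0.495/√0.75 = 0.572 and the current model has 90.3% power. Counting df only, adding T(-1) gives 91.4% at r = 0.2 and 92.7% at r = 0.3, gains of 1.1 and 2.4 points.

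**6. How large might r be?** Write a = corr(T(-1), T0), b = corr(T0, T2) and c = corr(T(-1), T2). Ignoring centre, r = (c − ab)/√((1 − a²)(1 − b²)).
- a = 0.7, b = 0.7, c = 0.5: r = (0.50 − 0.49)/0.51 = 0.02.
- a = 0.5, b = 0.5, c = 0.5: r = (0.50 − 0.25)/0.75 = 0.33.

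The same raw correlation of 0.5 with T2 BMI can therefore mean almost no gain or a useful one. The documents supply none of these correlations.

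**The case against.** The primary model has a strong defence. It matches the endpoint definition, which adjusts for baseline BMI with T0 as baseline, and the Sample size section, which counts one degree of freedom for the covariate and eight for centre. One baseline value plus the stratification factor is a standard confirmatory model, and randomisation makes the comparison unbiased without T(-1). All of this stands.

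Four stronger readings are tempting, and the documents support none of them.

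- *The plan contradicts itself because the two BMI models differ.* It does not. The mixed model is secondary and addresses the course of BMI from T1 to T3. Nothing says the two must share covariates.
- *The two models will give conflicting T2 effects.* The group contrasts predefined for the mixed model are T2−T1, T3−T1 and the average of T2 and T3 minus T1. It plans no T2 group difference to rival the primary estimate. The article lists no centre term for the mixed model, so adding T(-1) to the ANCOVA would not make the covariate sets identical either.
- *The primary test is the only analysis without T(-1) BMI.* Only the mixed model is said to use it; no covariates are listed for the other secondary analyses.
- *Precision is certainly being lost.* That depends on r, which is unknown. The relapse definition is scaled to BMI restored in hospital, but that is an outcome definition taken from earlier studies and does not show that inpatient gain predicts T2 BMI given T0.

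What remains is that the covariate is in hand, the sponsor uses it elsewhere for the same outcome, and including it risks very little.

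**Conclusion.** The point holds as a low-severity efficiency improvement. Under the assumed residual SD of 2.0 and two-sided alpha of 0.05, with 66 evaluable per arm, adding T(-1) BMI is worth about 0.4, 1.6 and 3.5 power points at partial r of 0.1, 0.2 and 0.3. Each figure is about 0.3 point lower if chance imbalance is charged, and the gain is smaller again if T0 BMI explains much of the variance. Below r of about 0.09 the expected effect is a trivial loss.

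These figures describe a complete-data comparison of 66 per arm. The actual primary analysis is intention-to-treat with imputation, so they are a guide to scale only.

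A reader might infer that the trial is underpowered or the planned number wrong. Neither follows: 66 per arm rests on an unadjusted t-test and needs no covariate gain.

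**What to change.** Before any unblinding, prespecify the primary analysis as an ANCOVA of T2 BMI on group, T0 BMI, T(-1) BMI and centre. Bring two statements into line with it: the endpoint's description of its adjustment, and the degree-of-freedom count under Sample size, where the covariates would use two degrees of freedom besides the eight for centre. If T(-1) BMI enters the analysis model, the imputation model should carry it too; the article does not describe that model, so this is a consequence of the change and not a criticism.

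The T0-and-centre model can be kept as a sensitivity analysis. If the sponsor prefers to keep it as primary, one sentence of reasoning would be enough. The cost of the change is one model term and one degree of freedom, with no new data and no change to the sample size.

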### Ethical aspects

The SUSTAIN trial is conducted in accordance with Good Clinical Practice (GCP-ICH guidelines). Ethical approval for conducting the trial has been obtained by each trial site’s ethics committee. All trial participants provide written informed consent prior to inclusion into the study. Patients can withdraw from the trial at any point without any disadvantage. We have established a Data Safety and Monitoring Board (DSMB) consisting of independent internationally renowned experts in the treatment of AN. The DSMB supervises the entire trial, with a specific focus on the occurrence of adverse events, and evaluates conformity of the trial with the study protocol and ethical standards.

## Discussion

The SUSTAIN trial addresses one of the most serious clinical problems in AN treatment namely early relapse following inpatient treatment, contributing to an unfavourable prognosis. In the present trial, we will investigate the efficacy of a novel post-inpatient psychotherapy specifically tailored to achieve sustained recovery in AN following inpatient or day-hospital treatment. To foster continuity of care, this novel treatment will predominantly be delivered via videoconference and compared to optimized treatment-as-usual (TAU-O) as a control condition [30]. The trial will provide evidence as to if the novel aftercare intervention contributes to a more favorable long-term course in patients affected by severe courses of AN.

In addition, we hope to also contribute with this trial to the field in several other ways: As outlined above, the concepts of recovery and relapse in EDs are currently used heterogeneously [9, 11, 12]; and we believe that with our data, we will be able to contribute to the current work and discussion towards an evidence-based consensus definition for recovery (and relapse) in AN. Secondly, we have implemented a participatory approach within the trial, which means that we have established a lived experience council which consists of people suffering from AN, people recovered from AN and carers of patients with AN. The council members accompany the entire trial, for instance, within the scope of regular council meetings and workshops, sharing their perspectives on needs and preferences of people affected by AN. The council gives advice on the conduct of the study and related processes, e.g. patient-friendly summaries and consent sheets, council members have been involved in the revision of the treatment manual, and they will also support in a later stage in patient- and carer-directed dissemination of results. Thirdly, our data will contribute to the evidence base on using technology-enhanced dissemination strategies to improve treatment access and continuity of care for ED patients. A recent systematic review summarizing findings from RCTs using e-Health interventions for ED patients concludes that the evidence is still very limited, with no trial reporting on the use of psychotherapy via videoconference [53].

We also face several challenges within the present trial: Patients with AN are often ambivalent towards treatment, and especially after completion of intensive inpatient treatment, patients could experience a certain tiredness or reluctance to continue with another treatment, which could influence the rate of aftercare uptake or attrition. However, in our feasibility pilot trial, 70% of eligible patients took up the post-inpatient relapse prevention and patients expressed a high subjective need for such interventions [26] which also motivated us to continue with an efficacy trial. As compared to the pilot trial, we have extended the dosage and duration of the aftercare intervention to the standard duration of outpatient treatment, both in the original treatment approach [28] and in the German health care system, and it remains to be evaluated if this results in more sustained outcomes. The trial has started simultaneously with the COVID-19 outbreak in Europe in spring 2020, posing practical and operational challenges for the conduct of a multicenter trial; and the ongoing pandemic with recurrent lockdown circumstances and high demands towards the health care system might influence recruitment. On the other hand, the dissemination of the treatment via videoconference is more timely then ever and enables us to provide a safe therapy environment under pandemic circumstances. Recent data have shown that people with AN are at risk of experiencing deterioration and relapse during the COVID-19 pandemic [54, 55], and the need to implement digital intervention and dissemination strategies to reach out to vulnerable patient groups has been emphasized [55, 56]. Moreover, whilst the COVID-19 crisis might act as a catalyst for the implementation of digitally assisted treatment delivery [57], evidence-based knowledge on the efficacy is nonetheless needed in order to provide safe and optimal digital mental health practices.

To summarize, we hope that the results from the SUSTAIN trial will contribute to the knowledge on effective aftercare interventions following inpatient treatment for adult patients with a severe form of AN and inform therapists on how this patient group can be supported towards sustained recovery.

## Data Availability

Not applicable.
